## Abstract

**Introduction:**

Almost 20 000 babies are born to teenage mothers each year in England, with poorer outcomes for mothers and babies than among older mothers. A nurse home visitation programme in the USA was found to improve a wide range of outcomes for young mothers and their children. However, a randomised controlled trial in England found no effect on short-term primary outcomes, although cognitive development up to age 2 showed improvement. Our study will use linked routinely collected health, education and social care data to evaluate the real-world effects of the Family Nurse Partnership (FNP) on child outcomes up to age 7, with a focus on identifying whether the FNP works better for particular groups of families, thereby informing programme targeting and resource allocation.

**Methods and analysis:**

We will construct a retrospective cohort of all women aged 13–24 years giving birth in English NHS hospitals between 2010 and 2017, linking information on mothers and children from FNP programme data, Hospital Episodes Statistics and the National Pupil Database. To assess the effectiveness of FNP, we will compare outcomes for eligible mothers ever and never enrolled in FNP, and their children, using two analysis strategies to adjust for measured confounding: propensity score matching and analyses adjusting for maternal characteristics up to enrolment/28 weeks gestation. Outcomes of interest include early childhood development, childhood unplanned hospital admissions for injury or maltreatment-related diagnoses and children in care. Subgroup analyses will determine whether the effect of FNP varied according to maternal characteristics (eg, age and education).

**Ethics and dissemination:**

The Nottingham Research Ethics Committee approved this study. Mothers participating in FNP were supportive of our planned research. Results will inform policy-makers for targeting home visiting programmes. Methodological findings on the accuracy and reliability of cross-sectoral data linkage will be of interest to researchers.

Strengths and limitations of this studyThis study will complement results from the Building Blocks trial in England, by evaluating the real-world effect of the Family Nurse Partnership (FNP) on a range of health, educational and social care outcomes up to age 7 years.The study cohort comprises joint trajectories for mothers and babies captured in Hospital Episode Statistics (HES; containing >97% births in England and information on subsequent healthcare use), with linked information from FNP programme data and the National Pupil Database (NPD; containing information on children’s and mothers’ educational attainment and social care).Evaluating outcomes for up to 31 000 FNP families and up to 1 million controls will provide statistical power to detect small differences, differences in rare outcomes and to perform subgroup analyses to determine whether the FNP is more effective in particular groups of families.No unique identifiers exist between HES and NPD databases, and linkage may be incomplete.Findings will inform the adaptation of the FNP and targeting of support for teenage and young mothers to specific subgroups.

## Introduction

Approximately 3% of babies each year (19 000 in 2018) are born to mothers aged below 20 in England and Wales.^1^ Teenage mothers are more likely to experience adversity and have rapid repeat pregnancies, and are less likely to be engaged with education and employment compared with older mothers.^2–5^ For their children, young maternal age is associated with higher incidence of preterm birth and low birth weight^6 7^ and a greater risk of child maltreatment and associated adverse long-term consequences including poorer physical, social, emotional and cognitive outcomes.^8–10^ These adverse maternal and child outcomes of teenage pregnancy, due to social adversity, disruption to education and employment, and child-rearing practices, are of major importance to public health research.^11 12^

The Family Nurse Partnership (FNP) is an intensive home visiting programme that aims to improve outcomes of pregnancies among vulnerable young mothers. Participants receive up to 64 home visits from early pregnancy until the child’s second birthday. Specifically, the FNP aims to improve birth outcomes, optimise child health and development and promote economic self-sufficiency among vulnerable mothers.^13^ Three randomised controlled trials in the USA found evidence of benefit on a number of maternal and child outcomes, including reductions in child maltreatment, child emergency department visits and subsequent births, as well as some improvements in child developmental outcomes and longer subsequent birth intervals.^14–18^ Effects on hospital visits for injury or maltreatment, children’s educational achievements and maternal educational qualifications were less consistent. A trial in the Netherlands found reduced child maltreatment reports by age 2,^19^ and a trial of a FNP-based model in Germany reported improved child development among high-risk women only, although no difference in subsequent births within 2 years.^20^ Non-randomised studies have reported reduced child maltreatment,^21^ infant death^22^ and subsequent births^23^ among FNP participants compared with controls, as well as different patterns of emergency room visits.^24^

Following evidence from the US trials, FNP was introduced in the UK in 2007. The FNP was rolled out via partnerships between local authorities (LAs) and healthcare organisations; to date, more than 130 LAs have implemented the programme. Teenage and young mothers who do not participate in the FNP receive usual care, consisting in comprehensive maternity care and at least five home visits by a health visitor, as well as a varying range of additional services;^25^ substantial variation in usual care exists between LAs.^26^ In England, the FNP was initially offered to pregnant teenagers aged under 20 years up to 28 weeks gestation, but since 2017, selected sites have expanded to include women up to 24 years with specific vulnerability criteria, and/or have implemented some personalisation of the programme.

Following trials in other countries, the Building Blocks trial randomised 1618 families in England between 2009 and 2010 and showed no benefit of FNP on primary outcomes up to the child’s second birthday (smoking in late pregnancy, birth weight, subsequent pregnancy or child A&E and hospital attendances).^27^ However, the interpretation of trial results was debated due to the choice of maternally reported early childhood development as a secondary outcome, for which a positive effect was observed, and strong support locally for the value of FNP on parent-child relationships.^28–30^ Follow-up has been extended up to the child’s seventh birthday, with a focus on child maltreatment.^31^

Evaluating complex interventions such as the FNP requires an understanding of the context in which they are delivered as well as the mechanisms of change, in order to investigate and interpret any differences in effects across contexts and populations.^32 33^ Indeed, differences in the comparator of usual care may explain differences in results between trials in the USA, England and the Netherlands; these may also vary over time and between LAs in England.^26 28^ Furthermore, evidence from the US trials suggests that the youngest, most disadvantaged mothers are likely to benefit most from FNP.^28^ Adequately powered subgroup analyses are needed to examine whether some groups of families benefited from FNP more than others. In addition, constrained conditions under which trials are conducted often do not match the complexity of real-world implementation of programmes.^34^

Linkage of existing administrative records provides a cost-efficient means of evaluating services as they are implemented in the real world, by bringing together data from different sectors on a range of outcomes. They also allow for a sufficiently large sample size for subgroup analyses. Our population-based study will use longitudinal observational data to evaluate effects on outcomes of mothers and children up to age 7 among eligible families and generate evidence on the factors that may influence effectiveness and programme engagement (including participant characteristics, setting, provider and programme delivery).^35 36^ Evaluating outcomes for up to 31 000 FNP families and up to 1 million controls will build on the results of the Building Blocks trial by providing increased statistical power to detect smaller differences, differences in rarer outcomes and subgroup differences for which the Building Blocks trial was underpowered. Study results will inform targeting of services and commissioning by generating evidence on which groups of mothers and their children benefit from the real-world implementation of FNP in England.

## Methods and analysis

### Study design and population

This study aims to evaluate the real-world, ongoing implementation of the FNP in England on the outcomes of mothers participating in FNP and their children, with the specific objectives of assessing (1) which groups of mothers receive FNP across LAs, (2) the effect of the FNP on maternal and child outcomes, including which families benefit most from FNP and (3) contextual factors influencing FNP programme effect. It will complement results from the Building Blocks trial in England,^27^ Building Blocks 2–6 year follow-up^31^ and evaluation of the FNP in Scotland using linked administrative data.^37^

We will create a retrospective cohort of all first-time mothers aged 13–24 years giving birth in England between 1 April 2010 and 31 March 2017 and their children, using individual-level, linked, longitudinal data from routinely collected hospital, education and social care records. Mothers up to 24 years will be included because some FNP sites modified inclusion criteria to include young mothers up to this age. The cohort will be created through linkage of hospital records (Hospital Episode Statistics (HES)), education and social care records (National Pupil Database (NPD)) and FNP programme data for mothers and their children. Our approach builds on previous linkage of education and health records and validated methods of linking hospital records for mothers and babies.^38 39^ The infrastructure and methodology used to create the linked database will be highly relevant for ongoing evaluation and monitoring of the FNP and other early interventions.

### Description of data sources

#### Hospital records: Hospital Episode Statistics (HES)

Hospital records for mothers aged 13–24 years and their children in England will be extracted from records of births and deliveries in HES. HES is a data warehouse containing details of all hospital admissions (from 1997), outpatient appointments (from 2003) and A&E visits (from 2010) at NHS hospitals in England.^40^ HES data have been used extensively in research. In addition to the birth record, we will link information from hospital admissions and A&E visits for mother and child (including up to 11 years before delivery for the mother, see online supplementary appendix). Information captured in HES includes administrative data (including admission dates, NHS trust, GP code), demographic information (including age, sex, ethnicity) and clinical information (diagnoses and procedures). A unique ‘HESID’ is assigned to enable episodes of care for the same individual to be combined. Diagnoses are coded by professional coders in hospitals using ICD-10 codes (International Classification of Disease, V.10); procedures are coded using OPCS-4 codes (Office of Population, Censuses and Surveys Classification of Surgical operations and procedures, V.4).^41 42^ Date and cause of death are obtained via linkage between HES and civil registration (deaths) data performed by NHS Digital. Based on previous methodological work, we will link delivery records for mothers and birth records for their children within HES to create a mother-baby HES cohort.^38^

10.1136/bmjopen-2020-038530.supp1Supplementary data

#### Education and social care records: National Pupil Database (NPD)

The HES cohort of mother-baby pairs will be linked to education and social care records from the Department for Education for both mothers and children in the FNP and control groups (including information before delivery for mothers). Information on assessments, attainment and progression at each key stage is available for all pupils in state schools in England, alongside eligibility for free school meals, information about special educational needs and information about absences and exclusions. NPD data, including social care data, have been used extensively in research.^43^

For both mothers and their children in the cohort, we will link HES data to the following NPD databases:

The yearly School Census (formerly PLASC), the Pupil Referral Unit (PRU) Census and Alternative Provision—including pupil-level information from 2002 for pupils aged 2–19+ on special educational needs, free school meal eligibility and information about absences and exclusions.The Children in Need Census (CINC)—including information on referrals to children’s social services, assessments carried out on these children and whether the children became the subject of a child protection plan, from 2008.^44^The Children Looked After (CLA) return—including information on all looked after children and recent care leavers in England, from 2005.^45 46^

For mothers only, we will link to Key Stages 2, 4 and 5 data, which includes teacher assessments and/or test results in Years 3–6 (ages 7–11), Year 11 (age 16) and Year 12/13 (ages 17–18). For children only, we will link to the Early Years Census and Early Years Foundation Stage Profile (EYFSP), including teacher assessments for 3 and 4 year olds (from 2008) and 2 year olds (from 2014), as well as to Key Stage 1 assessment data (ages 5–6).

A Unique Pupil Number (UPN) is used for linkage of CLA and CINC with the NPD. The UPN is usually assigned at first entry to a maintained school or nursery, typically around the age of four or five. Therefore, it is not possible to link the NPD to CLA data for children who are looked after only before they enter nursery/school or adopted children (who are provided with a new UPN).^47^ However, information on out-of-home care available for FNP participants at all ages will enable us to examine the scale of underestimation of out-of-home care before school in the administrative data.

#### Programme delivery: FNP Information System (FNP IS)

The HES cohort will be linked to the FNP IS to obtain information on participation in FNP. The FNP IS is a bespoke system that supports the implementation of the FNP programme in England, provided by NHS Digital under contract to the FNP National Unit on behalf of Public Health England. Data are reported in real time and are used locally by FNP teams and nationally by the FNP National Unit to monitor programme delivery and support quality improvement.

Data collected in the FNP IS include information from the mother and child collected at enrolment (by 28 weeks gestation at the latest, including mother’s age, marital status, living arrangements, education, employment, social care), 36 weeks gestation (including maternal health, alcohol, drugs and smoking), birth (including birth weight and gestational age) and at regular intervals until 24 months after birth (including child health and development, social care and other maternal baseline variables). Information on each visit is also collected (including date, length of visit, family nurse seen and referrals to other services). The FNP IS became functional in 2009, and data quality is reported to be high from 2010 onwards. FNP data have been used in previous research.^48 49^

FNP IS contains maternal and child identifiers at enrolment/birth: name, sex, date of birth, postcode, GP code and NHS number. When mothers graduate from the FNP, pseudonymised data are retained by the FNP National Unit only and identifiers are held solely on secure servers at NHS Digital. Since some identifiers might have changed since enrolment (eg, mother’s name, postcode), identifiers will first be updated using the Personal Demographic Service (PDS) within NHS Digital, so that the most relevant set of identifiers can be used for linkage.^50^

The time span covered by each data source (including look-back, study and follow-up periods) is described in the online supplementary appendix.

### Data linkage

Data flows are described in figure 1. Linkage of HES and FNP will be conducted by NHS Digital; linkage with NPD will be performed by the Department for Education. The linkage algorithm for each step (HES-FNP and HES-FNP-NPD) will be developed in an iterative process, taking into account the completeness of available identifiers (NHS number, GP practice, date of birth, sex, plus name for FNP participants) and building on existing strategies for linkage between HES and NPD. The quality of the linkage will be assessed by estimating the rates and distributions of linkage errors^39 51^ according to key maternal and child characteristics. Only deidentified data will be accessed by the research team, and the linked HES-FNP-NPD data will be securely stored on the Office for National Statistics Secure Research Service.

**Figure 1 F1:**
[figure not shown]
Data flows diagram. Note: items in italics are identifiers. CIN, Child in Need; CLA, Child Looked After; FNP, Family Nurse Partnership; GP, general practitioner; HES, Hospital Episode Statistics; NHS, National Health Service; NPD, National Pupil Database; ONS SRS, Office for National Statistics Secure Research Service; PDS, Personal Demographics Service; UCL, University College London.

### Outcomes of interest

Study outcomes are described in figure 2 and table 1. We selected outcomes for the FNP evaluation based on the FNP logic model,^52^ with some caveats outlined below. We will assess the FNP’s effect on child abuse and neglect, as measured by unplanned hospital admissions for injury or maltreatment-related diagnoses, child in need status, child looked after status and death. As the UPN for linking education and social care data is usually assigned at school entry, social care data for children only involved with social care prior to school entry cannot be linked. Therefore, we will only examine child in need and child looked after status after school starting age (4/5). We will also examine the FNP’s effect on other child outcomes including uptake and non-attendance for referral to outpatient departments, early years level of development, Key Stage 1 achievement, school attendance and Special Educational Needs status.

**Figure 2 F2:**
[figure not shown]
Family Nurse Partnership evaluation outcomes, data sources and selected maternal characteristics. HES, Hospital Episode Statistics; NPD, National Pupil Database.

**Table 1 T1:** Family Nurse Partnership evaluation outcomes and data sources

Domains	Outcomes	Years after birth	HES	NPD*	ONS
*Child outcomes (up to age 7)*					
Child abuse and neglect	Unplanned hospital admissions for any injury or maltreatment-related diagnosis (using ICD10 code lists)^66 67^ Discharge to social services at birth Child in care Child in need status Death	0–7 0 4/5–7 4/5–7 0–7	✓ ✓	✓ ✓	✓
Healthcare use	Unplanned hospital admissions (any diagnoses) A&E visits (any diagnoses) Referral to outpatient departments (uptake and non-attendance)	0–7 0–7 0–7	✓ ✓ ✓		
Education	Good level of development in early years assessment^68^ Key Stage 1 assessment SEN status School attendance	5 7 5–7 5–7		✓ ✓ ✓ ✓	
*Maternal outcomes*					
Maternal adversity	A&E visits (any diagnoses) Unplanned hospital admissions (any diagnoses, and for violence, self-harm or drug/alcohol abuse)^69^ Death	0–7 0–7 0–7	✓ ✓		✓
Reproductive outcomes	Subsequent deliveries within 18 months of index birth	0–2	✓		
Education	Key Stage 4 and 5 assessment† School attendance after birth‡	0–7 0–7		✓ ✓	

*Including the School Census, Child in Need Census and Child Looked After databases.

†Among mothers without Key Stage 4/5 attainment at birth.

‡School attendance information is collected up to age 15.

HES, Hospital Episode Statistics; NPD, National Pupil Database; ONS, Office for National Statistics; SEN, special educational needs.

Some healthcare use outcomes—A&E visits and unplanned hospital admissions for any diagnosis—will be reported as descriptive outcomes, since the direction of effect could be interpreted positively or negatively (FNP participation might reduce the need for emergency care or alternatively increase appropriate care-seeking). Nonetheless, they represent important outcomes for understanding the effects of FNP on care-seeking behaviour. Similarly, the potential for surveillance bias to distort the effect of early life interventions on child maltreatment has been discussed extensively:^19 27 53^ indeed, nurse home visiting results in increased contact with nurses, potentially leading to lower thresholds for reporting among participating families than control group families. This bias in ascertainment of maltreatment may dilute or reverse the association between FNP participation and maltreatment. Conversely, it has also been hypothesised that nurse’s closeness to participants may delay reporting of suspected maltreatment.^19^

Maternal outcomes will include unplanned hospital admissions for adversity-related reasons (violence, self-harm and drug/alcohol abuse) after birth and death. As for children, maternal rates of A&E visits and unplanned hospitalisations will be reported as descriptive outcomes. We will also examine the effect of FNP participation on school attendance and achievement after birth, and subsequent pregnancies within 18 months of the first birth ending in live or stillbirths. We will examine subsequent births from a pregnancy within 18 months (rather than 24 months as measured in the Building Blocks trial) because 18-month birth-to-pregnancy intervals are associated with the highest risks of adverse outcomes for women and babies.^54^ However, in addition to the outcomes in table 1, we will validate our findings against the outcomes reported in the Building Blocks trial by examining a range of birth outcomes and subsequent deliveries from pregnancies within 24 months of the index birth.

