### Sample size and power calculation

Exploratory analysis of HES data suggests that approximately 9.5% of children born to first-time teenage mothers are admitted to hospital for injuries by age 6. Assuming a baseline rate of 9.5% for the percentage of children with this outcome up to age 6, a total of 6798 children (3399 in each group) would be required to observe a significant relative reduction of 20% in hospital admissions for injuries, with 80% power and a 5% significance level. In our cohort, birth outcomes will be available for around 31 000 FNP births; 24 000 FNP families will have a full 3 years of follow-up and 9000 will have a full 6 years of follow-up. The number of control (never enrolled) families will vary for the propensity score and adjusted analyses; up to one million potential controls (corresponding to total births to women aged 13–24 between April 2010 and March 2017) will be available for these analyses.

Key Stage 4 and 5 assessment outcomes (for ages 14–16 and 16–18, respectively) will be examined among mothers who have not sat these examinations before giving birth. We estimate that the sample size for this subgroup will be around 1800 FNP mothers for Key Stage 4 and 13 000 for Key Stage 5.

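### Table 1 counts repeat deliveries within 18 months of the index birth; the text defines and justifies births from pregnancies beginning within 18 months, which needs about 27 months of follow-up for a term birth

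*Protocol article*

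**What the plan says.** Table 1 of the protocol article, under Reproductive outcomes, has one row: "Subsequent deliveries within 18 months of index birth". The column for years after birth reads 0–2 and the data source is HES.

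The text under Outcomes of interest describes the outcome differently, twice. It is first "subsequent pregnancies within 18 months of the first birth ending in live or stillbirths". Then: "We will examine subsequent births from a pregnancy within 18 months (rather than 24 months as measured in the Building Blocks trial"). The reason given for 18 months is that "18-month birth-to-pregnancy intervals are associated with the highest risks of adverse outcomes for women and babies". For validation against the Building Blocks trial, the same section adds "subsequent deliveries from pregnancies within 24 months of the index birth".

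That section opens by naming Figure 2 and Table 1 as the place where study outcomes are described. It presents the validation outcomes as additional to those in Table 1. Figure 2 is not shown in the material at hand.

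**The concern.** The table measures the time from the index birth to the next delivery. The text measures the time from the index birth to the start of the next pregnancy. The two differ by a full gestation, and nothing in the article reconciles them.

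An analyst who codes from Table 1, which the article names as the outcome list, would test a different and rarer event from the one the text justifies. Three things follow:

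- The rationale concerns pregnancies that begin up to 18 months after birth. The table wording leaves out about the second half of that interval for term births.
- The main outcome and the 24-month validation outcome would no longer share a clock. Under the text they differ by 6 months. Under the table, at delivery, they differ by about 15 months (18 against about 33).
- The data are retrospective, so two live definitions of one outcome leave room to choose between them after results are seen.

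**Working it through.** **The plan's own figure.** The only sample size in the article is for injury admissions: 9.5% against 7.6% (a 20% relative reduction), 80% power, 5% two-sided (assumed), equal groups. The two-proportion formula with pooled variance under the null and no continuity correction gives 3398.8, so 3399 per group and 6798 in total. That matches the article exactly. It does not bear on the repeat-birth outcome, for which no rate, event count or sample size is stated.

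**Follow-up needed under the text definition.** Formula: 18 months + gestation g, with one month = 365.25/12 days. Gestation is an assumption.

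| Gestation | g (months) | 18 + g | 24 + g (validation outcome) | 18 − g: latest start counted by Table 1 |
|---|---|---|---|---|
| 38 weeks (from conception, term) | 8.74 | 26.7 | 32.7 | 9.3 |
| 40 weeks (from last period, term) | 9.20 | 27.2 | 33.2 | 8.8 |
| 42 weeks (post-term) | 9.66 | 27.7 | 33.7 | 8.3 |

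A window that ends at 24 months contains the table's 18-month delivery outcome. It does not contain the text's outcome.

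**How many events differ.** Let L be a postpartum lag in which no conception occurs, and P the risk by 18 months of a conception that ends in a birth. With a constant hazard after the lag:

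- λ = −ln(1 − P)/(18 − L)
- F(t) = 1 − exp(−λ(t − L))
- ratio of text events to table events = P / F(18 − g)
- share of text events missed by a 24-month window = 1 − F(24 − g)/P

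Worked case: P = 0.20, L = 0, g = 9.

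- λ = 0.2231/18 = 0.01240
- F(9) = 0.1056, so the ratio is 0.20/0.1056 = 1.89
- F(15) = 0.1697, so the share missed is 1 − 0.1697/0.20 = 15%

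Results with P from 5% to 40%:

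| g (months) | L (months) | Ratio, text to table |
|---|---|---|
| 9 | 0 | 1.8–2.0 |
| 9 | 1.5 | 1.9–2.2 |
| 9 | 3 | 2.2–2.5 |
| 9 | 6 | 3.3–3.9 |
| 7 | 0 to 6 | 1.5–2.4 |
| 9.2 | 6 | 3.6–4.2 |

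At g = 9, a literal 24-month window misses about 13–25% of the text-definition events across these lags and risks.

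**Follow-up available.** The article gives about 31 000 FNP births, of which 24 000 "FNP families will have a full 3 years of follow-up and 9000 will have a full 6 years of follow-up". Three years is 36 months, which exceeds both 28 and 34. If births accrued evenly over the 84 months from April 2010 to March 2017 (assumed), that is 31 000/84 ≈ 369 a month. The stated counts then put the end of data between about April and September 2018:

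- 9000/369 ≈ 24 months of births, plus 72 = about 96 months after April 2010
- 24 000/369 ≈ 65 months of births, plus 36 = about 101 months after April 2010

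On that basis, moving from 18 to 28 months of complete follow-up loses about 10 × 369 ≈ 3 700 FNP families. The actual time spans are in an appendix that is not shown.

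**The case against.** The intended definition can be recovered. The text states it twice, its rationale uses the same interval, and so does the validation outcome. Only one compressed table row disagrees, and the article promises a detailed statistical plan before analysis. This stands as to size: it is an internal inconsistency with a cheap remedy, not a flaw in the design. It does not remove the point, because the article fixes one outcome in two incompatible ways and names the table as its outcome list. That is different from leaving detail to a later plan.

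A reader might also infer stronger things that the documents do not support:

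- *That the text definition doubles the events, as a fact.* The article gives no repeat-birth rate and no distribution of intervals. A factor near 2 follows only from an assumed constant hazard with little or no lag.
- *That the outcome becomes underpowered.* With an assumed 20% risk under the text and 10% under the table, detecting a 10% relative reduction takes about 6,040 and 13,500 per group respectively. Both are well below the 24 000 FNP families with three full years and the up to one million potential controls, and no stated power calculation rests on this outcome.
- *That 0–2 years fits neither definition.* The column is in whole years and does contain an 18-month delivery outcome. It falls short only of the text definition.
- *That repeat births are otherwise unmeasured.* It is the only reproductive row in Table 1, but the 24-month validation outcome is also planned and is on the pregnancy clock.

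**Conclusion.** The point holds as a contradiction that changes what is measured. Table 1 and the text define different repeat-birth outcomes, and the 0–2 year window does not cover the one the text justifies. Two results need only a gestation length: follow-up to about 27 months for a term birth (nearly 28 at 42 weeks), and a table definition that reaches only pregnancies starting in about the first 9 months.

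The direction of the difference is certain, since every delivery counted by the table also comes from a pregnancy begun within 18 months, while the reverse is not true. Its size is not: about 1.5 to 4 times as many events under the text definition, depending on gestation, postpartum lag and risk, none of which the documents give. Feasibility and stated power are not at risk. The text and its rationale agree with each other, so the table row is the item to correct.

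**What to change.** Change the Table 1 row to: *Delivery (live or stillbirth) from a pregnancy beginning within 18 months of the index birth*. Date the start of pregnancy as delivery date minus gestational age. Replace the 0–2 year entry with a window long enough for term and post-term births, about 28 months, and state about 34 months for the 24-month validation outcome. Cut-offs of exactly 27 and 33 months would be too short: at 40 weeks the table above gives 27.2 and 33.2 months, so some qualifying term and post-term births would be lost. Censor or exclude mothers whose HES follow-up is shorter, and say which.

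The cost is one table row and the censoring or loss of the most recent births (about 3 700 FNP families relative to an 18-month window, if accrual was even). The definition also relies on gestational age at the later delivery. The article does not say how complete that item is, so a rule for missing values is needed.
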